**Table 1 Tab1:** **Study variables**

**Instrument**	**Assessment area**	**Time of assessment**	**Applied by**
MINI Neuropsychiatric interview	Psychiatric diagnosis	Baseline	Researcher A
PHQ-9	Severity of depression	Baseline and follow-up sessions*	Researcher A (baseline) Online (follow-up sessions)
Sociodemographic data	Gender, age, marital status, education, occupation, economical level	Baseline	Researcher A
SF-12 Health Survey	Health-related quality of life	Baseline and follow-up sessions*	Online
CRSI	Health and social services use	Baseline and 6 and 12 post-treatment months	Researcher A (baseline) Researcher B (6 and 12 post-treatment months)
EQ-5D	Health related quality of life	Baseline and 6 and 12 post-treatment months	Online
PANAS	Positive and negative affect	Baseline and 6 and 12 post-treatment months	Online
FFMQ	Facets and factors of mindfulness	Baseline and 6 and 12 post-treatment months	Online
PHI	Remembered and experienced well-being	Baseline and 6 and 12 post-treatment months	Online

*Follow-up sessions: Post-treatment, 6 and 12 post-treatment months.

#### Main outcome

The primary outcome will be depressive symptom severity assessed via PHQ-9 [34] using the Spanish validated version [29]. This is an instrument for diagnosis and measuring the severity of depression. PHQ-9 is brief and it is completed by the patient. It will be registered at four times: baseline, post-treatment, 6 month follow-up, and 12 month follow-up.

#### Secondary outcomes

Sociodemographic variables. Relevant sociodemographic information regarding gender, age, marital status (single, married/relationship, separated/divorced, and widowed), education (years of education), occupation, economical level will be collected.

Mini-International Neuropsychiatric Interview (MINI). This is a short structured diagnostic psychiatric interview that yields key DSM-IV and ICD-10 diagnoses [35]. MINI can be administered in a short period of time and clinical interviewers need only a brief training. It will be registered at baseline using its Spanish validated version [33].

SF-12 Health Survey [36]. This instrument consists of 12 items that measure the health-related quality of life. A psychometric analysis suggested that it has adequate psychometric properties and a validated Spanish version [37].

Client Service Receipt Inventory [38] (CSRI-Spanish version) [39]. Questionnaire for collecting information about use of healthcare and social care services and other economic impacts (such as time off work due to illness). The variant used in this study was designed to collect retrospective data on service utilization during the previous months after the last assessment. Data on baseline assess the previous six months before inclusion.

EuroQoL-5D questionnaire (EQ-5D – Spanish version) [40]. Generic instrument of health related quality of life. It has two parts: Part 1 records self-reported problems in each of five domains: mobility, self-care, usual activities, pain/discomfort and anxiety/depression. Each domain is divided into three levels of severity corresponding to no problems, some problems and extreme problems, which allows obtaining a population-based preference score or societal index (SI). A total of 243 theoretically possible health states can be obtained and the SI is calculated on the basis of these health states. Values range from 1 (best health state) to 0 (death). However, this index may also provide negative values that correspond to health states perceived as worse than death-. Utility scores for these health states were assigned using the readily available Spanish population tariffs [41]. Part 2 records the subject’s self-assessed health on a VAS, a 10 cm vertical line on which the best and worst imaginable health states score 100 and 0 respectively.

Positive and Negative Affect Scale (PANAS) [42] PANAS consists of 20 items that evaluate two independent dimensions: positive affect (PA) and negative effect (NA). The range for each scale [10 items on each] is 10 to 50. The instrument’s psychometric properties are quite satisfactory. It has a validated Spanish version [43].

Five Facet Mindfulness Questionnaire (FFMQ) [44]: This questionnaire comprises 39 items that assess five facets or factors of mindfulness: observing (8 items), describing (8 items), and acting with awareness (8 items), not judging inner experience (8 items) and not reacting to inner experience (7 items). Items are rated using a Likert scale that ranges from 1 (“never or very rarely true”) to 5 (“very often or always true”). The Spanish version of this scale has been validated [45] and has been shown to have good internal consistency and reliability.

The Pemberton Happiness Index (PHI) [46]. This instrument consists of eleven items related to different domains of remembered well-being (general, hedonic, eudaimonic and social well-being) and ten items related to experienced well-being (positive and negative emotional events that possibly happened the day before). A psychometric analysis suggested that it has adequate psychometric properties and a validated Spanish version [46].

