### Interventions

All interventions (except ITAU) are composed of one face-to-face group session and 4 online, individual and interactive therapeutic modules.

Face-to-face session will involve 3-5 patients and will be 90 minutes in length. The aim of this session will be to explain the program structure and main components of treatment, and to motivate participants for change.

The online therapeutic modules are oriented to work on different psychological techniques and the duration of each module will be approximately 60 minutes. All modules include an explanation of the module contents, check questions to test if they understand the contents and exercises to practice such techniques. These modules are sequential, in order to move step by step, all along the program. However, user can review the module contents once they are finished. Duration of the program can vary among users, it is estimated the duration for most people will be 4-8 weeks. The participants will receive two weekly-automated mobile phone messages, encouraging them to proceed with the program and reminding them of the importance of doing the tasks in each module. Furthermore, the participants will receive an automated e-mail encouraging them to continue with the modules if they have not accessed the program for a week. The program also offers continued feedback to users through the assessment tools showing them their progress throughout the entire treatment process.

All groups of patients will receive treatment as usual improved by their GPs, as described below in this section. All groups of patients will also receive a participant manual with information about technical aspects of the online program.

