### Analysis strategy

#### Analysis of clinical efficacy

Intention-to-treat and per-protocol analysis will be used. Analysis will include the description and “head-to head” comparison between the four groups. Descriptive statistics of the included variables (mean and 95 per cent confidence interval for normally distributed quantitative variables; and median and interquartile range for abnormally distributed quantitative variables) will be performed. To confirm main hypothesis, all variables will be compared (t0-tk) using an analysis of variance (ANOVA) and post-hoc tests or Kruskal-Wallis non-parametric tests. Finally, more sophisticated multivariate analysis, including multilevel regression, will be used. The effect size of improvement and intention-to-treat (ITT) will be estimated.

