#### Descriptions of costing procedure

Data collection on the use and utilization of health and social services will be collected through the questionnaire Client Service Receipt Inventory (CSRI) Spanish version [40]. The variant to be used in this study was designed to retrospectively collect data on service use during the previous 6 months.

Costs were estimated from the healthcare and societal perspectives during the six months of follow-up. Direct health care costs were calculated by adding the costs derived from medication consumption, medical tests, use of health-related services, and cost of the staff running the CBT intervention.

The cost of medication will be calculated by determining the price per milligram according to the Databases of the drug from the Ministry of Health and Consumer and included the value-added tax. The total costs of medications were calculated by multiplying the price per milligram by the daily dosage used (in milligrams) and the number of days that the treatment was received. The main source of the unit cost data for medical tests and health services will be use the OBLIKUE database of health care costs. The OBLIKUE database contains information about Spanish healthcare service costs and was derived by systematic reviews of the literature; it consists of approximately 18,000 entries.

Indirect costs (lost productivity): Lost productivity will be calculated using the human capital approach, which involves multiplying the minimum daily wage in Spain for 2014 by the number of days of sick leave, as reported by each patient. Finally, total costs were calculated by adding the direct and indirect costs. Unit costs are expressed in Euros (€) based on 2014 prices.

In our study the general guidelines for conducting pharmacoeconomic analyzes in Spain and the International Society for Pharmacoeconomics and Outcomes Research (ISPOR) [47,48] will be followed.

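### The CSRI recall window is stated two ways: one reading makes the first follow-up window longer than baseline, the others leave the programme weeks unrecorded

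*Protocol article*

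**What the plan says.** The Protocol article describes the CSRI recall period in two places. Secondary outcomes says the variant in this study collects "retrospective data on service utilization during the previous months after the last assessment", and adds: "Data on baseline assess the previous six months before inclusion". Descriptions of costing procedure says the variant was "designed to retrospectively collect data on service use during the previous 6 months".

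Table 1 gives the CSRI at baseline (Researcher A) and at 6 and 12 months after treatment (Researcher B). It is not given at the end of treatment. That visit does exist for the PHQ-9 and SF-12, whose schedule the footnote defines as "Follow-up sessions: Post-treatment, 6 and 12 post-treatment months". On programme length, the Interventions section says that "it is estimated the duration for most people will be 4-8 weeks".

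Analysis of clinical efficacy states that "all variables will be compared (t0-tk) using an analysis of variance (ANOVA) and post-hoc tests" or a non-parametric alternative. The costing section multiplies unit prices by days of medication and the minimum daily wage by days of sick leave. The Cost-utility analysis section forms an incremental ratio of costs to QALYs, with QALYs taken as an area under the curve.

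**The concern.** Both sections describe one instrument, so only one recall rule can be on the form. The two rules coincide only where the gap being counted is exactly six months. Follow-up is timed from the end of treatment and no CSRI is taken there, so the gap between the first two CSRIs is six months plus the length of the programme.

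Visits, medication days and sick-leave days are counts that grow with the length of the window. If windows differ between visits and totals are compared unadjusted, unchanged behaviour looks like a change. If windows are held at six months, the treatment weeks drop out of the record, and costs no longer cover the period that starts at baseline. Either way the service-use outcome and the economic analysis are affected. The PHQ-9 primary outcome is not.

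**Working it through.** The article gives no calculated figure to reproduce here. The check is calendar arithmetic.

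**Inputs**
- Baseline window: 6 months (Secondary outcomes).
- CSRI times: baseline, then 6 and 12 months after treatment (Table 1).
- Programme length *p*: 4-8 weeks for most users (Interventions).
- One month = 365.25/12 = 30.44 days, so *p* = 28/30.44 = 0.92 months to 56/30.44 = 1.84 months.

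**Reading A: the last assessment is the last CSRI**
- First follow-up window = 6 + *p* = 6.92 to 7.84 months.
- Ratio to baseline at a constant rate of use = (6 + *p*)/6 = 6.92/6 = 1.153 to 7.84/6 = 1.307, an apparent rise of 15-31%.
- Second follow-up window = 12 - 6 = 6 months, a ratio of 1.00. The distortion is confined to the first follow-up.
- No time after baseline goes unrecorded.

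**Reading B: the last assessment is the post-treatment visit, or the window is a fixed 6 months**
- First and second follow-up windows = 6 months each, so the built-in rise is 0%.
- Unrecorded time between baseline and the end of treatment = *p* = 0.92 to 1.84 months.
- Share of the interval from baseline to the first follow-up CSRI = *p*/(6 + *p*) = 0.92/6.92 = 13% to 1.84/7.84 = 24% (0.235).
- Share of the whole span from baseline to the last CSRI = *p*/(12 + *p*) = 0.92/12.92 = 7% to 1.84/13.84 = 13%.

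| | First window (months) | Rise against baseline at constant use | Unrecorded share of first interval |
|---|---|---|---|
| A: since last CSRI | 6.92-7.84 | 15-31% | 0% |
| B: fixed 6 months, or since post-treatment visit | 6 | 0% | 13-24% |

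Reading B also bears on the cost-utility ratio. Table 1 takes the EQ-5D at the same times as the CSRI. An area under the curve that starts at baseline therefore runs through the programme weeks, while the CSRI costs skip them. Staff time for delivering the intervention is a separate cost item, so the gap concerns other service use, medication and sick leave.

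**The case against.** The strongest reply is that the two sections can be read as agreeing. The post-treatment visit is a study assessment. If it is the last assessment before the 6-month visit, the window is six months, as the costing section says, and nothing is inflated. This stands. A reader might infer from the Secondary outcomes wording that service use must rise at the first follow-up, but the text does not support that. It follows only if the last assessment means the last CSRI. That is the more natural meaning, because no CSRI is taken at post-treatment, but it is not stated. The agreement between sections comes at the price of the unrecorded programme weeks.

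The forecast dates also point away from unequal windows. Recruitment ends in July 2015 and monitoring in July 2016, twelve months later, which would fit follow-up counted from inclusion and equal six-month windows. These dates are only a forecast, and they do not fit the post-treatment timing given under Instruments and in Table 1. They do not settle the matter.

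Next, the baseline comparison sits under clinical efficacy, whereas the CSRI has its own costing and cost-utility sections. This stands in part. The comparison reaches the CSRI only because it is written for all variables and the CSRI is listed among the secondary outcomes. In the incremental cost ratio, a window common to all arms adds no false difference in use between them, so 15-31% is not an effect on the ICER.

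A reader might also infer that the programme arms have longer windows than the control arm (ITAU). The article does not show this. ITAU has no modules, and its post-treatment date is not defined. If its visits match the programme schedule, the difference is zero. Equal windows are not secured, but a difference by arm is not established.

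Finally, rate conversion is normally left to an analysis plan. That is fair, and its absence is not the complaint. The complaint is that two stated recall rules conflict.

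**Conclusion.** The point holds in limited form. The article states two recall rules for one instrument and, with follow-up timed from the end of treatment, neither is free of cost. Counting from the last CSRI gives a 15-31% apparent rise in raw totals at the first follow-up only. A fixed six-month window, or one from the post-treatment visit, gives no rise but never records 13-24% of the first interval.

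These sizes assume the stated 4-8 week programme, visits held on schedule and, for the rise, a constant rate of use with unadjusted totals. Programmes outside that range would move them. No bias between arms is claimed. The issue concerns a secondary outcome and the economic analysis, and it should be settled before the first follow-up CSRI, because recall periods cannot be reliably repaired after collection.

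**What to change.** - Reconcile Secondary outcomes and Descriptions of costing procedure into one rule: each follow-up CSRI runs from the date of the previous CSRI to the current date. Print both dates on the form and record the window length.
- Time the ITAU assessments on the same schedule from randomisation as the programme arms, so that windows are comparable by design.
- Express service use and sick leave per month of window only when comparing with the baseline CSRI.
- For the ICER, do not use monthly rates. Use costs accumulated from baseline over the same period as the QALYs.

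The cost is small: changed form wording, one recorded variable, and a recall period at the first follow-up that is longer by about one to two months. No extra visits are needed.

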### Ethical aspects

A general overview of the aims and characteristics of the study and the interventions will be provided to the patients. They will also be informed that they will be participating voluntarily, and that they can choose to withdraw at any time with the guarantee that they will continue to receive the treatment considered most appropriate by their GP. Informed consent will be obtained from the participants before they are aware of which group they are to be included in. For ethical reasons, patients allocated to Treatment as Usual will be offered the possibility to complete the psychotherapy program. The study follows national and international norms (Helsinki Convention and the Declaration of Madrid of the World Psychiatric Association). The Study Protocol was approved by the Comité d’Ètica de la Investigació de les Illes Balears (CEI-IB) (ref: IB 2144/13 PI).

An important issue in a study using ICTs is participants’ data protection. In order to protect personal information, AES (*Advanced Encryption Standard*) strategies regarding the use of personal passwords and data encryption will be followed.

### Analysis strategy

#### Analysis of clinical efficacy

Intention-to-treat and per-protocol analysis will be used. Analysis will include the description and “head-to head” comparison between the four groups. Descriptive statistics of the included variables (mean and 95 per cent confidence interval for normally distributed quantitative variables; and median and interquartile range for abnormally distributed quantitative variables) will be performed. To confirm main hypothesis, all variables will be compared (t0-tk) using an analysis of variance (ANOVA) and post-hoc tests or Kruskal-Wallis non-parametric tests. Finally, more sophisticated multivariate analysis, including multilevel regression, will be used. The effect size of improvement and intention-to-treat (ITT) will be estimated.

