### Sample size

According to the literature, with a standard deviation (SD) of 9.2 and a mean of 16.2 in the control group (ITAU) [30], 14.59 in the positive affect group [31], 16.12 in the healthy lifestyle group [32] and 10.3 in the mindfulness group [30], accepting an alpha of 0.05 and a beta risk < 0.2 in a bilateral contrast, and assuming a 25% patient loss to follow-up, we need 60 subjects in each condition. Therefore, the total sample size was determined at 240. This sample size also allows calculating clinically significant difference in the main outcome variable, PHQ-9 [29], and this difference has been placed at 5 points.

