## Discussion

Brief psychotherapy is an effective alternative for depression treatment to offer in primary care [18]. Moreover, the effectiveness of Internet-delivered psychotherapy for this disorder has also been demonstrated [24]. Low-intensity psychological interventions applied by Information and Communication Technologies (ICTs) are not frequently used in Spain and could be an efficacious and cost-effective therapeutic option for the treatment of depression. The strength of the study is that, to our knowledge, this is the first multicenter controlled randomized clinical trial of four low intensity and self-guided interventions applied by ICTs (healthy lifestyle psychoeducational program; focused program on positive affect promotion; brief intervention based on mindfulness; and improved treatment as usual group) in Primary Care settings.

Two important limitations of the study will be the negative attitudes from GP to recommend this treatment and dropout rates in treatment groups (significantly greater than in the control group according to previous studies). Efforts to maintain dropout rates in the range of 30% and training sessions for participating GPs will be carried out to overcome these limitations.

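### The confirmatory ANOVA or Kruskal-Wallis test, if run on observed scores, is not full intention-to-treat, and the unequal dropout the protocol expects puts it at risk of bias

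*Protocol article*

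**What the plan says.** The section on analysis of clinical efficacy opens with "Intention-to-treat and per-protocol analysis will be used". It then assigns the main hypothesis to one family of tests: "To confirm main hypothesis, all variables will be compared (t0-tk) using an analysis of variance (ANOVA) and post-hoc tests or Kruskal-Wallis non-parametric tests". The model-based analysis comes after this: "Finally, more sophisticated multivariate analysis, including multilevel regression, will be used". The section does not say how patients without a follow-up score enter the intention-to-treat analysis.

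Two other sections bear on missing data. The sample size section applies a single loss rate to all arms: "assuming a 25% patient loss to follow-up, we need 60 subjects in each condition", and "the total sample size was determined at 240". The Discussion names as a limitation "dropout rates in treatment groups (significantly greater than in the control group according to previous studies", and its response is "Efforts to maintain dropout rates in the range of 30" per cent, together with training of GPs. The main outcome section and Table 1 schedule the PHQ-9 for all patients at baseline, post-treatment, 6 and 12 months, with follow-up scores collected online.

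**The concern.** A t0-tk comparison needs a score at both times. On observed data, an ANOVA or Kruskal-Wallis test at a given tk therefore covers only the patients seen at that tk. Someone who answered post-treatment and at 6 months but not at 12 months contributes nothing to the 12-month test. The label says intention-to-treat, while the population analysed would be those who were followed.

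This would matter less if loss were equal and unrelated to outcome. The article itself expects more dropout in the treatment groups than in control. If those who leave differ in mean change from those who stay, unequal loss shifts the programme-versus-ITAU contrast away from the randomised comparison. The method that uses all available repeated scores is already listed, but it is not the one said to confirm the hypothesis.

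**Working it through.** **Inputs from the article.** 60 patients per arm, 240 in total; 25% loss to follow-up (sample size section); dropout to be held to about 30%, and higher in treatment groups than in control (Discussion); SD 9.2 and a clinically significant difference of 5 points (sample size section). The article gives no figure for the dropout gap or for how leavers differ from completers, so both are assumed below.

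**The plan's own figure.** There is no stated bias to reproduce. The nearest figure, 60 per arm, does not follow from 25% loss. Mindfulness versus ITAU (16.2 − 10.3 = 5.9) needs 39 evaluable per arm, and 39/0.75 = 52. A four-group ANOVA on the stated means needs 42, and 42/0.75 = 56. With 30% loss, 42/0.70 = 60. This may be coincidence and does not decide the present point, but it is a further reason to reconcile the two rates.

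**Formula.** In an arm with dropout fraction d, let D be the mean improvement of completers minus that of leavers. The full-arm mean is (completer mean) − d × D, so the completer mean overstates it by d × D. With D equal across arms:

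bias = (d_programme − d_ITAU) × D

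**Assumed gap.** If 25% is the overall loss and 30% the loss in each of the three programme arms, ITAU loss x satisfies (3 × 30 + x)/4 = 25, so x = 10. The gap is 20 points. In patients: 3 × 18 + 6 = 60, which is 25% of 240.

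**Result by D.**
- D = 0: bias 0.
- D = 2.5: 0.20 × 2.5 = 0.5 points (10% of 5).
- D = 5: 0.20 × 5 = 1.0 point (20% of 5).
- A negative D reverses the sign.

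**Simulation.** One million patients per arm, no true effect, SD 9.2 at both times, assumed baseline-to-follow-up correlation 0.5, completers only. Patients with the highest value of a dropout score are lost. That score is pure noise, baseline plus noise, or unseen follow-up plus noise. Entries are bias in mean t0-tk; positive favours the programme.

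| Dropout, programme vs ITAU | Completely at random | Driven by baseline severity | Driven by unseen follow-up score |
|---|---|---|---|
| 25% vs 25% | −0.02 | −0.02 | 0.03 |
| 30% vs 20% | 0.02 | −0.47 | 0.48 |
| 30% vs 10% | 0.00 | −0.97 | 1.00 |
| 35% vs 10% | 0.02 | −1.23 | 1.21 |

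If the more severe patients leave, the remaining programme patients start lower and have less room to improve, so the bias runs against the programmes. If those doing badly at follow-up leave, it favours them.

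**Dependence on the assumptions.** In this set-up the bias is proportional to SD × (1 − correlation), here 9.2 × 0.5 = 4.6. The article does not say on which scale the SD of 9.2 was measured. Its entry limit of a PHQ score below 14 allows a baseline SD of at most 13/2 = 6.5. With 6.5 at both times, the 30% vs 10% figures shrink to about 1.0 × 6.5/9.2 = 0.7 points either way.

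**The case against.** The strongest reply is that the observed-cases reading is inferred. The article never says the ANOVA uses observed scores only; it plans intention-to-treat alongside per-protocol, and either named test can be run on imputed data. A condensed article may leave missing-data rules to a full protocol or SAP that is not shown, so its silence on imputation is no fault in itself. This stands, and it is why the point is conditional. What remains is a stated choice: the article gives the confirmatory role to a test that does not use a patient's other visits, and gives none to the model that does.

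It can also be said that the final place of multilevel regression marks sequence and not rank. That is possible, but only the ANOVA/Kruskal-Wallis sentence is tied to confirming the hypothesis.

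Third, dropout in the Discussion may mean leaving the programme and not missing the PHQ-9. This also stands. Follow-up scores are collected online, so stopping the modules may lead to missed assessments, but need not.

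A reader might go further and infer that the result will be biased in favour of the programmes because those who do not benefit leave. The documents do not support that: they give no reasons for leaving, unequal dropout alone creates no bias, and baseline-driven loss pushes the other way. Nor can one combine a large gap between arms with a loss of 25% to 30% in every arm: with 30% and 10%, a programme arm loses 18 patients and ITAU loses 6.

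**Conclusion.** The point holds in conditional form. The test named as confirmatory, if run on observed scores, is not a full intention-to-treat analysis, and the imbalance in dropout that the protocol expects puts its comparison with ITAU at risk of bias. The bias is zero if loss is completely at random. With an assumed 20-point gap it is roughly 1 PHQ-9 point in either direction, about 20% of the 5-point clinically significant difference, and less if the SD is below 9.2. The gap, the mechanism and the correlation are assumptions; the article fixes only that dropout is expected to be greater in the treatment groups. The documents do not show that the trial's result will be biased, or in which direction.

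**What to change.** In the section on analysis of clinical efficacy:

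- Name the multilevel repeated-measures model, already planned, as the primary intention-to-treat analysis: PHQ-9 at post-treatment, 6 and 12 months; arm, time and arm-by-time; patients analysed as allocated.
- Use baseline PHQ-9 as a covariate or, to retain patients who have a baseline score only, as part of the outcome vector. Either form deals with loss that depends on baseline severity, provided the model is adequate.
- Add one delta-adjusted sensitivity analysis in which unobserved scores in the programme arms are shifted for the worse, since the primary model does not protect against loss driven by the unseen outcome.
- Keep ANOVA/Kruskal-Wallis as supportive.
- Reconcile the 25% loss to follow-up in the sample size section with the roughly 30% dropout in the Discussion, and say whether the latter means leaving the programme or missing the PHQ-9.

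No new data collection is needed, because the PHQ-9 is already scheduled for all patients at every follow-up. The cost is wording, a little more analysis, and reliance on missing at random in the primary model. The change should be made before outcome data are seen.
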